## 6.2 PROCEDURES DURING THE SCREENING PERIOD

### 6.2.1 INFORMED CONSENT

At the screening visit, participants will have the opportunity to ask questions and have a full discussion of the information provided in writing and/or visually and verbally. This will include the following key messages:

- ▶ That there is a 1 in 3 chance that they are assigned to a placebo injection, but this may change during the trial to 1 in 2 if one of the trial arms is discontinued or interrupted
- ▶ That we do not know if the active vaccine combination regimens will prevent HIV
- ▶ That condoms and PrEP are known to reduce the risk of acquiring HIV when used or taken consistently
- ▶ That pregnancy is to be avoided until 18 weeks after last vaccine as the safety of vaccines is not known
- ▶ That the immune responses made by their bodies to the vaccines could show up in future HIV tests

Participants will be shown images of the PrEP pills. They will be asked if they discussed their participation with anyone and if any problems arose because of this. If they wish to proceed, they will be given an informed consent form to read and sign prior to any investigations. It will be dated and countersigned by the investigator or delegated person, who explained the study to them. If they are unable to read and write, they will be asked to place their thumbprint on the informed consent in the presence of an independent witness who has been present for the discussion. The witness cannot be a member of the site study staff.

A copy of the consent form will be provided to the participant and one copy kept in the study file according to local procedures. If they have not already done so, they will be encouraged to discuss their participation with their partners, friends and family.

### 6.2.2 ELIGIBILITY

After informed consent has been collected, a unique trial identifier will be assigned by the study staff.

To assess eligibility demographic information, a past and current medical history, details of current and recent medication including use of PrEP and herbal remedies will be collected during a structured interview. The interview will be conducted by a member of the study team and recorded on the appropriate CRF, which will be identified by the unique study number. The number will be allocated to the participant after consent has been collected. Details of contraception and sexual history will be collected to assess the risk of pregnancy arising in the participant or their partner, and the risk of HIV acquisition respectively. Participants who are using condoms or taking PrEP consistently are not considered at risk of acquiring HIV. Therefore they would not comply with eligibility criteria 5. Details of smoking, use of alcohol and recreational drugs will also be collected as these can impact on the risk of HIV, the strength of immune responses and lead to abnormal routine laboratory parameters.

The screening examination will include weight (kg), height (cm), , blood pressure, pulse, respiratory rate, inspection of the skin at the injection site, respiratory, cardio-vascular, abdominal, and neurological examination. An assessment of cervical, axillary and inguinal lymph nodes will also be undertaken.

### 6.2.3 INVESTIGATIONS

Blood (as per [Table 1](#)) will be collected for point of care HIV testing. A sample will also be sent to the local laboratory for testing in accordance with the HIV testing algorithm in the LAP. Residual from the sample will be stored in case it is necessary to conduct additional HIV tests to assist with the statistical analyses.

Blood will be collected for analysis of the following routine laboratory parameters in the local laboratories and recorded in the appropriate CRF:

- ▶ Haemoglobin
- ▶ Alanine aminotransferase, aspartate aminotransferase, alkaline phosphatase, bilirubin
- ▶ Glucose
- ▶ Creatinine and estimated glomerular filtration rate using the Cockcroft-Gault formula
- ▶ hepatitis B surface antigen (screening only)
- ▶ RPR (and TPHA if required)

A first pass urine specimen will be collected from men and from women, and sent to the local laboratory to screen for gonorrhoea and chlamydia. If indicated by the sexual history participants may be asked to provide a rectal swab. Staff will explain how to collect the swab and participants will be able to do so in private.

Urine will be collected for a point of care test to detect tenofovir. Any discrepancies between the result of the test for tenofovir and self-report will be explored with the participant and recorded on the CRF.

For female participants of childbearing potential a pregnancy test will be performed by analysis of a urine sample for Human Chorionic Gonadotrophin (HCG).

## 6.3 PROCEDURES AT ENROLMENT

This visit should take place within 8 weeks following the screening visit. If more than 8 weeks have elapsed study staff should consult the SOM to find out which screening assessments need to be repeated.

### 6.3.1 ELIGIBILITY

Study staff will check that participants understand the key messages contained in the information sheet and listed in [section 6.2.1](#).

Study staff will review the routine laboratory parameters and screen for STIs collected at screening and determine whether there are any clinically relevant abnormalities that require further investigation prior to randomisation. STIs will be treated appropriately, but the participant can proceed to randomisation on the day, if otherwise eligible.

Participants will review any new adverse events or new medications since the screening visit and for female participants, any changes in contraception. All this information will be recorded on the appropriate CRF according to the SOM. The Risk assessment CRF will also be administered.

Study staff will review the risk of the participant acquiring HIV again to see if anything has changed since screening, and conduct a point of care HIV test in accordance with the LAP.

For female participants of childbearing potential a pregnancy test will be performed by analysis of a urine sample for Human Chorionic Gonadotrophin (HCG) and a negative result will be confirmed before each injection.

The review of Eligibility will be completed using the appropriate CRF.

Prior to randomisation, blood will be collected for 4th generation ELISAs, and to store for future immunological assays, HIV RNA, and intracellular tenofovir diphosphate levels.

### 6.3.2 RANDOMISATION

Eligible participants will be randomised in a concurrent 3 x 2 factorial design to

- ▶ one of three injection regimens in a 1:1:1 ratio (the placebo group will be randomised 1:1 to match the volume of the protein injection in the combination arms)
- ▶ TDF/FTC or TAF/FTC

Study staff will be able to generate the randomisation code electronically and add the unique randomisation identifier to the prescription together with the unique trial identifier to take to pharmacy to prepare the appropriate products for injection and dispense PrEP. In the event that the database is not available for example due to internet problems, study staff will write the prescription using the trial identifier only and take this to pharmacy. The pharmacist will be able to access the code manually or via telephone, and add this to the prescription, providing study staff with the appropriate PrEP agent to give to the participant and two products for injection, one in each arm.

### 6.3.3 INJECTION

Prior to injection, study staff will conduct an assessment relevant to the solicited adverse events described in section 6.5, and record the details on the appropriate CRF. This will include vital signs, a measurement of temperature, and inspection of the site where injections will be administered in each arm.

The injection will be labelled so that study staff can identify which arm the product is to be injected into. They will not know whether the product is active or placebo.

Study staff should administer the injection into the deltoid muscle of the designated upper arm and record this in the appropriate CRF including the time of injection.

The DNA/placebo vaccine is 1ml in volume and should be injected into the deltoid muscle of the left arm. The MVA/placebo is 1ml in volume and is slightly opaque and should be injected into the deltoid muscle of the left arm. The two protein/placebo vaccines are of 1ml for AIDSVAX® B/E/placebo and 0.45ml for CN54gp140 in MPLA-L/placebo and should be injected into the deltoid muscle of the right arm. All syringes will be covered throughout the trial with a label to obscure the contents but the volume will be revealed to clinic staff because of the position of the plunger. It will therefore be possible for staff to differentiate between 1 and 0.45ml but they will not be able to differentiate between active and placebo injection.

In the event that study staff administer the product into the opposite muscle to the one intended a deviation should be noted (see SOM for details).

Following injection participants should remain in clinic for up to 60 minutes, in order to assess solicited adverse events at 25-60 minutes following injection. Study staff will go through the **Vaccine diary cards** with participants and explain how and when to complete these over the following 7 days.

### 6.3.4 PREP

Participants should be given 60 tablets at weeks 0 (visit 2) in order to have sufficient supply to last 30 days beyond their next scheduled dispensing visit at week 4

Study staff will review the **PrEP diary cards** with participants. They will ensure that participants understand when they are at risk of exposure to HIV and know how long it takes for PrEP to become effective.

They will review any concerns the participant has about side-effects from PrEP and medicines in general. They will advise the participant how to remember to take a tablet every day by linking this to a daily routine.

Participants will be asked whether they have informed partners, friends and family since the screening visit, and whether any issues arose. If they have not informed the other people they live

with, they will be asked how they plan to store the drug and whether they have concerns about others finding it.

## 6.4 TREATMENT PROCEDURES DURING FOLLOW-UP

Injections will be administered at visits 4, 8 and 12 from randomisation according to the schedule in [Table 1](#). PrEP will be dispensed at visits 4 and 7. Additional PrEP may be required at other weeks or at an unscheduled visit to ensure drug continues for two weeks after the third injection.

### 6.4.1 INJECTIONS

Study staff should follow the procedures outlined in [section 6.3.3](#) with respect to assessments prior to injections, administration of the injections, and assessments after the injections in clinic. The information should be recorded on the appropriate CRF.

Study staff should endeavour to administer the injections in the period between the earliest timepoint and upper target, as defined in [table 1](#). Provided the visit is within the latest timepoint window outlined the injections may proceed without further consultation. Study staff should complete a protocol deviation form if the injection occurs after the upper target window..

### 6.4.2 PREP

Study staff should follow the procedures outlined in [section 6.3.4](#) with respect to an assessment of understanding of risk and discussion of concerns.

Participants should be given 60 and 90 tablets at visits 2 and 4 in order to have sufficient supply to last 30 days beyond their next scheduled dispensing visit at visits 4 and 7. Additional drug may need to be dispensed at other visits including an unscheduled visit to ensure the participant has enough to last for 2 weeks after the third injection. See [section 5.5.5](#).

For safety and adherence assessments, see [sections 6.5.4 and 6.6](#) respectively.

## 6.5 PROCEDURES FOR ASSESSING SAFETY OF TRIAL TREATMENTS

### 6.5.1 SOLICITED ADVERSE EVENT ASSESSMENT

Vaccines are associated with a number of well-characterised local, systemic and laboratory reactions referred to as solicited adverse events ([Table 7](#)). These adverse events will be purposively collected during the structured interview, examination and laboratory testing.

Local and systemic assessments will take place on the day of each injection at the following time points: before the injection, and 25- 60 minutes after the injection. Participants will receive two injections at every time point. The local adverse events will be specific to each arm, but the systemic ones will only be recorded once and will be timed against the second injection.

Participants will be provided with **Vaccine diary cards** to assist collection and grading of adverse events that start within 7 days of the injection.

Follow-up of solicited adverse events may occur at a clinic visit or through a phone-call one week after the injections at visits 3 and 5 respectively and at a visit 2 weeks after 3rd and 4th vaccines (visits 9 and 13 respectively). Study staff will go through the list of solicited adverse events in a structured interview and record these together with grade on the appropriate CRF. If any of the events reported on the phone are still moderately severe (grade 2) or worse, participants will be invited to the clinic for review.

Blood (14mls) for routine safety parameters will be collected 4 weeks after the 1st and 2nd injections at visits 4 and 6, and 2 weeks after the 3rd and 4th injections at visits 9 and 13 and at any other study

visit if required to confirm or follow-up an abnormal result for one of the listed parameters in **Table 7**. If the total bilirubin is elevated, study staff will request a result for conjugated bilirubin in order to grade the abnormality and determine any action to be taken with respect to further investigation and interruption to the vaccine schedule.

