### 6.1 TRIAL ASSESSMENT SCHEDULE

The trial assessment schedule consists of a screening visit (visit 1), an enrolment visit which must take place within 8 weeks of the screening visit and which defines week 0 (visit 2).

The first injection will take place at week 0 (visit 2) and further injection visits are at visits 4, 8 and 12. The latest timepoint that the second, third and fourth injection visit can take place is indicated in Table 1 and is the end of the 13th, 40th and 68th week from enrolment respectively. Visits 3, 5, 6, 9, 10 and 13 have specific activities and procedures that relate to the collection of key safety and efficacy variables following the injection visits and the ideal timing relates to each injection. The earliest timepoint and upper target for visits is also given in Table 1. Provided visits occur in the period between the earliest timepoint and upper target there is no need to complete a protocol deviation form. If the participant has passed the upper target for the visit, a protocol deviation form should be completed.

Safety follow-up visits (or calls) to ask about all adverse events are at visits 3,5-7,9-11,13-15. After visit 15, follow-up visits will continue every 12 weeks for HIV testing through to the end of the trial, and participants will be asked about any serious illness or admission to hospital at these visits. These visits will continue to the last 3 months of the trial when everyone will have a final study visit. Additional visits may be undertaken if indicated, for example to investigate or follow-up an adverse event or abnormal laboratory result.

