**Table 7: Solicited Adverse Events**

| TYPE                                                                                                                                          | EVENT                                                                                                                                                                                 |             |
|-----------------------------------------------------------------------------------------------------------------------------------------------|---------------------------------------------------------------------------------------------------------------------------------------------------------------------------------------|-------------|
| Local AEs within 7 days
(injection site)                                                                                                   | Pain or tenderness
Itching
Redness
Swelling (soft)
Induration (hard)                                                                                                      |             |
| Systemic Clinical AEs within 7
days of injections                                                                                          | Temperature
Chills
Myalgia/flu-like general muscle aches
Arthralgia
Malaise (excess fatigue)
Headache
Nausea
Vomiting
Generalised rash
Generalised itching |             |
| Systemic Laboratory AEs
4wks after 1 st & 2 nd injections
2wks after 3 rd & 4 th injections | Creatinine
ALT/AST
Alkaline phosphatase
Total bilirubin
Glucose                                                                                                           | Haemoglobin |

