### 6.5.2 OTHER ADVERSE EVENT ASSESSMENT

Information on other adverse events will be collected through an open question about health at study visits 2-15. Study staff will record the diagnosis or the signs/symptoms if a diagnosis is not apparent, the date of onset and the date of resolution if appropriate. If the event is ongoing, it may be appropriate to conduct a symptoms directed examination. After visit 15, staff will only collect and record information on serious adverse events at every 12 weekly visit.

Events should be graded according to the Division of AIDS (DAIDS) Table for Grading the Severity of Adult and Paediatric Adverse Events version 2.1, July 2017.

(<https://rsc.niaid.nih.gov/sites/default/files/daidsgradingcorrectedv21.pdf> ).

The relationship to injection or PrEP will be determined by the investigator according to the definitions provided in **Section 7**.

All of this information will be recorded on the appropriate CRF.

In the event that the participant is unable to attend a safety follow-up visit for personal reasons, the interview may be conducted on the telephone or at a home visit if the participant is agreeable.

Study staff will make every effort to follow adverse events to resolution or stabilisation in order to report the information on the appropriate CRF during the trial.

After the trial has closed and the database has been locked, additional information regarding serious adverse events that comes to the attention of the study staff should be reported by email to the CI and MRC/UVRI and LSHTM using the TSG email.

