##### 9.2.1.B Secondary

- ▶ Grade 3 and above solicited adverse events which last more than 72 hours
- ▶ Grade 3 and above laboratory adverse events that are confirmed on repeat testing if possible
- ▶ An adverse event leading to a clinical decision to discontinue or interrupt the product schedule, regardless of relationship
- ▶ Serious Adverse Events (SAEs)
- ▶ Other clinical and laboratory adverse events
- ▶ Binding antibodies to CN54gp140 and AIDSVAX® B/E gp120

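### Table 1 allows the solicited-event contacts at visits 3 and 5 from day 3, so the only structured interview after injections 1 and 2 can close before the 7-day window ends

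*Protocol*

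**What the plan says.** Section 6.5.1 gives diary cards "to assist collection and grading of adverse events that start within 7 days of the injection", and section 6.3.3 has staff "explain how and when to complete these over the following 7 days". Table 7 fixes the same period for local reactions ("Local AEs within 7 days") and for systemic clinical reactions.

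The route to the CRF is an interview: "Study staff will go through the list of solicited adverse events in a structured interview and record these together with grade on the appropriate CRF". After injections 1 and 2 it takes place at a clinic visit or "through a phone-call one week after the injections at visits 3 and 5 respectively". After injections 3 and 4 it takes place at visits 9 and 13, two weeks after the injection.

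Table 1 agrees on the targets (week 1 for visit 3, V4+1 for visit 5). Its row for the earliest timepoint reads 1-4d for visit 3 and V4+3d for visit 5. Section 6.1 then says: "Provided visits occur in the period between the earliest timepoint and upper target there is no need to complete a protocol deviation form".

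One secondary safety outcome of the vaccine trial (section 9.2.1.B) is "Grade 3 and above solicited adverse events which last more than 72 hours". The same event is a ground for interrupting the vaccine schedule in section 5.2.7 and a notable event for 24-hour reporting in section 7.2.

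**The concern.** Three parts of the protocol do not fit together. Table 7 and the diary define a 7-day window, and section 6.5.1 puts the interview at the end of it. Table 1 lets the interview happen when less than half of that window has passed, and section 6.1 treats this as ordinary compliance. A site that phoned every participant on day 3 would need no deviation form.

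What is at stake is the completeness of reactogenicity data after injections 1 and 2. If a reaction starts on day 5 and the contact was on day 3, no later step in the protocol requires staff to ask about it from the structured list or to read the finished diary. Visits 9 and 13 cannot be held before day 7, so the gap is confined to the first two injections.

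**Working it through.** No sample-size or error-rate formula applies. The check is calendar arithmetic on Table 1, in days after the preceding injection.

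**1. The stated timing.** The target row reproduces section 6.5.1: visit 3 at week 1 is day 7, and visit 5 at V4+1 week is day 7. The earliest row does not. For visit 3, 1 week minus 4 days is 7 - 4 = day 3. For visit 5, V4+3d is day 3. I read 1-4d as week 1 minus 4 days because the visit 5 entry is unambiguous and gives the same day. Read as days 1 to 4, it would be earlier still.

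**2. All four solicited-event contacts.** Days not yet observed = 7 - contact day, or 0 from day 7 on.

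| Contact | Earliest | Target | Upper target | Days of the 7 not yet observed at the earliest contact |
|---|---|---|---|---|
| Visit 3 (injection 1) | day 3 | day 7 | day 14 | 7 - 3 = 4 |
| Visit 5 (injection 2) | day 3 | day 7 | day 14 | 7 - 3 = 4 |
| Visit 9 (injection 3) | day 7 | day 14 | day 28 | 0 |
| Visit 13 (injection 4) | day 7 | day 14 | day 28 | 0 |

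At visits 3 and 5 a contact on day 3, 4, 5 or 6 leaves 4, 3, 2 or 1 days unobserved. At the limit this is 4/7 = 57% of the window. The no-deviation range, days 3 to 14, has 12 days, and 4 of them (days 3 to 6) fall before day 7.

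**3. The next scheduled contact after a day-3 interview.**

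- Visit 4: earliest week 3 = day 21, target day 28, upper target week 7 = day 49, latest end of week 13 = day 91. Gaps: 21 - 3 = 18, 28 - 3 = 25, 49 - 3 = 46, 91 - 3 = 88 days.
- Visit 6: earliest V4+3 weeks = day 21, target day 28, upper target day 35. Gaps: 18, 25 and 32 days.

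**4. What those later visits collect.** Section 6.5.2 says: "Information on other adverse events will be collected through an open question about health at study visits 2-15". That is an open question, not the solicited list. Visit 4 also has a check before injection 2 that is relevant to solicited events (sections 6.3.3 and 6.4.1: vital signs, temperature, injection sites), but the protocol does not say that it looks back over the first 7 days. Visit 6 has no injection and so no such check.

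**5. The 72-hour element.** A day-3 contact is nominally 3 × 24 = 72 hours after injection. If the clock times of injection and contact differ by up to 8 hours (an assumption), the elapsed time is 64 to 80 hours. A reaction that began at injection is at the threshold and may be just past it. Day 7 does not settle duration for every event either: a reaction that starts on day 7 passes 72 hours only after day 10. Duration therefore depends on follow-up at either contact time. What the earlier contact adds is the unobserved onset days.

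**The case against.** The strongest case is that this is a mismatch in window wording with little consequence. The target for both visits is one week and day 3 is only the outer allowance. A contact on days 7 to 14 loses nothing, and the protocol gives no basis for saying how many contacts would fall on days 3 to 6. Participants keep a contemporaneous 7-day diary, so late onsets need not rest on memory. Section 6.5.1 brings phone-reported events still at grade 2 or worse into clinic, and section 6.5.2 asks for onset and resolution dates and for follow-up to resolution or stabilisation. The operations manual, which is not shown, may require a later diary review.

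Most of this stands and limits the size of the point. It does not remove it. Follow-up to resolution helps only reactions known at the contact; it cannot find one that starts afterwards. The diary is an aid to collection, and the protocol names no step after an early contact at which the finished card is read.

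Three stronger readings are tempting, and the protocol does not support them.

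- A reader might infer that a day-3 visit cannot record an event of more than 72 hours. Step 5 shows this is only nominal, and an event still present is to be followed.
- A reader might infer that the secondary outcome is undercounted in the active arms, or biased between arms. The windows are the same in all arms, and clinic staff are blind to active versus placebo. No undercount is shown.
- A reader might infer that prime and boost reactogenicity are confounded with observation time. The safety objective compares each regimen with placebo, and the protocol plans no comparison of injections 1 and 2 with injections 3 and 4.

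**Conclusion.** The point holds as an internal inconsistency with a limited consequence. Table 1, section 6.5.1 and Table 7 cannot all govern as written. A compliant contact on days 3 to 6 ends the structured solicited-event interview with 1 to 4 of the 7 days unobserved, and the next scheduled collection is at least 18 days after a day-3 contact. Later onsets may be missed or recorded only through an open question.

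This is a risk of incomplete capture, in all arms alike, for a secondary safety outcome after two of the four injections. The primary safety outcome is defined differently, and power and type I error are unaffected. The conclusion rests on reading 1-4d as week 1 minus 4 days, and on the operations manual not adding a later structured diary review. Its size in practice depends on how many contacts fall before day 7, which the protocol does not allow one to estimate.

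**What to change.** Reconcile Table 1 with section 6.5.1 and Table 7 in one of two ways.

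- **Move the window.** Set the earliest timepoint of visit 3 at day 7 and of visit 5 at V4+1 week, matching visits 9 and 13 (V8+1 and V12+1), and keep the upper targets. The cost is a narrower no-deviation range, days 7 to 14 (8 days) instead of days 3 to 14 (12 days), so some contacts may newly need a deviation form.
- **Keep early contacts and add a review.** State in section 6.5.1 that after a contact before day 7, staff go through the completed 7-day diary against the solicited list, with onset and resolution dates, after day 7 and no later than visit 4 (injection 1) or visit 6 (injection 2). The cost is one extra diary review for each early contact.

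Under either option, reactions still present at the contact need their resolution date recorded under section 6.5.2, because neither a day-3 nor a day-7 contact settles the 72-hour criterion for late onsets.
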